## Appendix 5 A detailed study statistical analysis plan

The primary analysis of the primary outcome (as well as secondary outcomes b, c, d, e, f, h, i, and j) will be an unadjusted Mann-Whitney test. As a sensitivity analysis the *p* values will be recalculated using permutations within groups defined by site and the presence/absence of hypertension. This test is a non-parametric version of an ANOVA adjusted for site and presence/absence of hypertension. A total of 100,000 permutations will be conducted for each test. The effect sizes will be quantified by direct comparisons of the raw means between groups. Confidence intervals will determined by non-parametric bootstrapping to accommodate the highly non-normal distribution of the outcomes.

The secondary endpoint “a” will be assessed by a Cox model treating death before normalization of lactate as a competing event. The Cox model will be adjusted for site and presence/absence of hypertension. The effect size will be quantified using the adjusted hazard ratio.

The secondary outcome “g” will be assessed using Fisher’s exact test. Effect sizes will be analyzed using crude proportions along with standard normality approximation-based confidence intervals.

The exploratory endpoint (90-day survival) will be assessed using Fisher’s exact test. Effect sizes will be quantified using odds ratios from a logistic regression adjusted for site and the presence of hypertension. As a sensitivity analysis a Cox model of time to death will also be employed. The Cox model will be adjusted for site and the presence/absence of hypertension. Here, the effect size will be quantified using the adjusted hazard ratio. The assumption of proportional hazards will be assessed using Schoenfeld residuals. Finally, Kaplan-Meier plots will be produced.

If any of the tests presented above must be based on data with more than 5 % missing multiple imputation will be employed. If just one test needs to be based on multiple imputation all tests will be conducted both as complete case analysis and multiple imputation. However, only for tests based on data with more than 5 % missing will the multiple imputation approach constitute the primary analysis. The multiple imputation will be conducted in R using the mice package and the recommendation in accordance with recommendations in the documentation of this package. All outcome variables (secondary and primary), sex, and age as well as stratification and treatment variables will be included in the multiple imputations procedure.

In all tests a *p* value of less than 0.05 will be considered statistically significant. It is noted that as the adaptive sample size recalculation is not depended on a particular value of the treatment effect at the time of recalculation, there is accordingly no need to adjust the significance level to take a possible adjustment of sample size into account. All analyses will be conducted in the statistical software package R. The full statistical analysis will be conducted blinded to actual treatment allocation and a full blinded statistical report produced. Of note, un-blinding will first happen after the full statistical report has been finalized.

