**Methods/design:**

The targeted tissue perfusion versus macrocirculation-guided standard care in patients with septic shock (TARTARE-2S) trial is a prospective, two-parallel-group, randomized, open-label, multicenter trial with assessor-blinded outcome evaluation. We will randomize at least 200 patients with septic shock in four European intensive care units (ICUs) to test whether a tissue perfusion-guided treatment strategy based on capillary refill time, peripheral temperature, arterial lactate concentrations, and accepting lower MAP levels, leads to a faster resolution of shock than macrocirculation target-guided standard care.

The primary outcome measure is days alive in 30 days with normal arterial blood lactate (first value of <2 mmol/L) and without any inotropic or vasopressor agent. Secondary outcomes include individual components of the primary outcome, days alive without renal replacement, days alive without mechanical ventilation in 30 days, and new acute kidney injury. The sample size enables detection of a 13.5-h difference in the primary outcome with a type 1 error of 5 % and power of 80 %, assuming 25 % mortality and a mean of 650 h (SD 30) among the 30-day survivors. After 150 included patients the statistician masked for allocation group will recalculate the sample size potentially increasing the sample up to 300. The Data Safety and Monitoring Board (DSMB) will review the safety data after 100 patients.

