### Statistical methods

The study flowchart is included as Fig. 1. A Mann-Whitney test for differences in continuous outcomes including the primary outcome measure, and Fisher’s exact test for dichotomous variables will be done as a primary analysis. A sensitivity analysis in subgroups of patients with and without previous hypertension will be performed. The components of the primary outcome measure (time to normalization of lactate, time to stopping of all vasoactive drugs, and day-30 mortality) are all included among secondary outcomes. In all tests a *p* value of less than 0.05 will be considered statistically significant. If missing data are >5 %, multiple imputations will be performed. A detailed statistical analysis plan is provided in Appendix 5.

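### For sparse yes/no adverse reactions (secondary outcome j), the planned bootstrap interval can have zero width, and two sections name different tests

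*Protocol article*

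**What the plan says.** The section Secondary outcome measures does not letter its items in the text at hand. The order matches Appendix 5: a is time to lactate normalization (Cox model) and g is new acute kidney injury (Fisher's test). The tenth item, j, is therefore the adverse reactions. It lists seven named reactions, from ventricular arrhythmia to limb ischemia, plus total serious adverse reactions, and the totals are to be given both as patients and as reactions. So j holds a yes/no variable per patient and a count per patient.

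Appendix 5 places all of j in one group with the main endpoint: "as well as secondary outcomes b, c, d, e, f, h, i, and j) will be an unadjusted Mann-Whitney test". For that group, "The effect sizes will be quantified by direct comparisons of the raw means between groups", and "Confidence intervals will determined by non-parametric bootstrapping to accommodate the highly non-normal distribution of the outcomes". The type of bootstrap is not named. The same paragraph adds, as a sensitivity analysis, p values from permutation within site and hypertension strata.

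Statistical methods in the main text assigns tests by type of variable. The first rule is "A Mann-Whitney test for differences in continuous outcomes including the primary outcome measure". For yes/no variables it names a different one: Fisher's "exact test for dichotomous variables will be done as a primary analysis". For every test a p "value of less than 0.05 will be considered statistically significant".

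**The concern.** The yes/no part of j falls under two rules. Statistical methods points to Fisher's test, and Appendix 5 points to Mann-Whitney. Appendix 5 itself uses Fisher's test and crude proportions for the other dichotomous secondary outcome, g.

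The interval matters more. A bootstrap resamples only what was observed, so it cannot produce an event in an arm that had none. For a reaction seen in few or no patients, the interval then understates the uncertainty, at the extreme to nothing.

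This group carries weight because the section on severe adverse reactions says that serious adverse events are not recorded as an entity and that the main ones are captured through the secondary outcomes and daily SOFA scores. Outcome j is thus one of the main safety comparisons of a strategy that accepts lower arterial pressure.

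**Working it through.** **Inputs from the protocol.** Sample size: "We will randomize at least 200 patients with septic shock", "potentially increasing the sample up to 300". With 1:1 allocation (assumed) this is 100 to 150 per arm. Alpha is 0.05, taken as two-sided because the protocol does not say.

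**Assumed inputs.** Event rates of 0.5 % to 10 %, because the protocol gives none, and the percentile form of the bootstrap.

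**The plan's own figure.** No figure is stated for j. The nearest is Table 1: 194 patients for 80 % power at 25 % mortality and 18 h among survivors. Simulating as described (log-normal, mean 70 v 52 h, SD 30, deaths set to 0, Mann-Whitney, 10,000 runs) gives 79.1 % at 194 and 80.1 % at 200. The sample size reproduces and is not in question.

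**Step 1: no events in either arm.** Every resample is all zeros, so the difference is always 0 and no form of bootstrap can give a width. The Wilson upper limit for 0/n is z²/(n + z²). At n = 100 this is 3.84/103.84 = 3.7 %, so the Newcombe interval is ±3.7 points. At n = 150 it is 3.84/153.84 = 2.5 %, giving ±2.5 points. With rate p in both arms, the chance of 0 v 0 for one reaction is (1 − p)^(2n):

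- 100 per arm: 0.995^200 = 37 %; 0.99^200 = 13 %; 0.98^200 = 2 %.
- 150 per arm: 0.995^300 = 22 %; 0.99^300 = 5 %.

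**Step 2: few events, 100 per arm.** Intervals are in percentage points. Mann-Whitney is asymptotic and tie-corrected.

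| Events | Bootstrap | Newcombe | Mann-Whitney p | Fisher p |
|---|---|---|---|---|
| 0 v 0 | [0, 0] | [−3.7, 3.7] | undefined | 1.00 |
| 0 v 3 | [0, 7] | [−1.2, 8.5] | 0.083 | 0.246 |
| 0 v 4 | [1, 8] | [−0.4, 9.8] | 0.044 | 0.121 |
| 0 v 5 | [1, 10] | [0.3, 11.2] | 0.024 | 0.059 |

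Check for 0 v 5. Without continuity correction, Mann-Whitney has z² = (N − 1)(ad − bc)²/[n₁n₂m(N − m)], where m is the total number of events. This is 199 × 500²/(100 × 100 × 5 × 195) = 5.10, so z = 2.26 and p = 0.024. Fisher's p is 2 × C(100,5)/C(200,5) = 0.059.

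**Step 3: coverage.** Exact binomial weights were applied over all likely tables, 100 per arm.

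| True rates | Bootstrap | Newcombe |
|---|---|---|
| 0.5 % v 1 % | 62 % | 99.9 % |
| 0.5 % v 2 % | 86 % | 99.6 % |
| 1 % v 2 % | 86 % | 99 % |
| 1 % v 3 % | about 94 % | 98 % |
| 2 % v 5 % | about 96 % | 97 % |
| 5 % v 10 % | about 96 % | 96 % |

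The reason is simple. If the arm with the higher true rate has no event, the upper limit is at most 0 and the interval misses. That alone happens with probability 0.99^100 = 37 % at a 1 % rate and 0.98^100 = 13 % at 2 %, which caps coverage at 63 % and 87 %.

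At 150 per arm, coverage is 75 % (0.5 % v 1 %) and 92 % (1 % v 2 %). With equal rates from 0.5 % to 10 % at 100 per arm it is 96 to 99.8 %. For overdispersed reaction counts with a mean of 0.2 to 0.4 per patient it is 94 to 95 %. For a count as sparse as 0.005 v 0.01 per patient it falls to 62 % again.

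**Step 4: is Mann-Whitney invalid on 0/1 data?** At 100 per arm its type I error is 0.2 % to 5.2 % for rates of 0.5 % to 10 %. It is not meaningfully inflated.

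**The case against.** A reader might infer that all of j is wrongly analysed, that Mann-Whitney is an invalid test here, or that the intervals are always too narrow. The documents support none of these.

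- Outcome j also counts reactions. Fisher's test is prescribed only for dichotomous variables, so nothing contradicts a rank test for counts.
- Mann-Whitney on 0/1 data keeps its type I error. The opposing p values largely reflect Fisher's conservatism: its type I error is 0.5 % at a 2 % rate and 2.1 % at 5 %, against 4.0 % and 4.4 % for Mann-Whitney.
- The permutation p value in Appendix 5 is the same kind of conditional test as Fisher's. An unstratified permutation gives 0.059 for 5 v 0, as Fisher does. The stratified version will differ somewhat, but a Fisher-like result would stand beside each Mann-Whitney p value.
- Low event rates are an assumption. Atrial fibrillation is on the list and need not be rare.
- The main text defers to Appendix 5 for detail, and Appendix 5 names j, so an analyst would know which rule to follow.
- Nothing says that an interval of [0, 0] would be read as proof of no difference. The event numbers would be reported beside it.

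All of this stands, and it reduces the test question to a matter of consistency. It does not rescue the interval: the permutation check yields a p value only, and following Appendix 5 as written still gives a zero-width or too narrow interval for sparse yes/no reactions.

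**Conclusion.** The point holds for the patient-level part of j and is minor.

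The substantive error is the interval. At 0 v 0 events it has no width, whatever the bootstrap type, against about ±3.7 points for Newcombe at 100 per arm. Where true rates are about 2 % or less and unequal, percentile-bootstrap coverage at 100 per arm is about 62 to 86 %. These coverage figures rest on assumed rates, 1:1 allocation and the percentile form. At 2 % v 5 % and above, with equal rates, or for total reaction counts, coverage is near nominal, so the defect must not be stated for the whole outcome.

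The difference between Statistical methods and Appendix 5 on the test is an inconsistency that can move a result across 0.05. It is not a validity problem. The primary analysis and the sample size are unaffected.

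**What to change.** In Appendix 5, split j into two parts.

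1. **Patients with at least one event, for each reaction:** report the numbers and the risk difference with a score-type interval (Newcombe or Miettinen-Nurminen) in place of the bootstrap. Name one test here and in Statistical methods. Fisher's test agrees with the main text.
2. **Reactions per patient:** keep the rank test and the bootstrap for the per-patient count.

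The cost is a short edit and no new data. The score-type interval is wider and conservative when events are very few. Choosing Fisher's test has a real price in power: at 100 per arm, 31 % against 49 % for Mann-Whitney at 1 % v 6 %, and 37 % against 49 % at 2 % v 8 %. The choice should be made knowingly, since these are safety comparisons. What matters most is that one test is named before the data are seen.

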### Randomization

Randomization will be done using a computer-based algorithm created by an independent statistician, to allow immediate and concealed allocation to the intervention arm. The patients will be stratified according to the site and presence/absence of chronic hypertension (with known medication). A varying block size will be used. Each patient will be allocated a unique patient ID-number. Randomization is targeted to be performed within 2 h after fulfillment of the inclusion criteria in the ICU (but no later than 4 h, the fulfillment of which is an exclusion criterion).

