### Statistical plan and data analysis

#### Sample size and power

We assume 25 % mortality in both study groups, and this phase II trial will be unlikely to have the power to detect any mortality difference between the intervention groups. Therefore, a surrogate endpoint (days alive in 30 days with normal lactate and without vasopressors) combining survival, need for vasopressor therapy, and normalization of hyperlactatemia has been chosen. A post-hoc analysis from the FINNAKI study in a similar study population revealed a 30-day mortality rate of 25 %, and in 98 patients (of 128) who survived the mean time alive without vasopressors or hyperlactatemia within 30 days (720 h) was 650 h (SD 35) (unpublished data).

In the power analysis we assumed that the time with vasopressors or hyperlactatemia among the 30-day survivors follow a log-normal distribution with mean of 70 h (70 minus “treatment effect among survivors for the TTP group”) and SD 30, this simulated value was subtracted from 720 h (the number of hours in 30 days). For each configuration of sample size, mortality rate and expected treatment effect we simulated data and compared the two groups using a Mann-Whitney test. Ten thousand simulations were done for each configuration to compute the power. The required sample sizes (both groups combined) to achieve 80 % power as a function of mortality proportion (i.e., fraction of patients with a zero value for the primary endpoint) and average change in the primary endpoint among survivors are displayed in Table 1.

**Table 1 Tab1:** Power calculations

	Change among survivors in hours (and among all patients)		
Mortality proportion	12 h (9 h)	18 h (13.5 h)	24 h (18 h)
20 %	340	156	90
25 %	438	194	118
30 %	562	270	158
35 %	660	348	210
40 %	660	456	282

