## Appendix 4 Data to be registered

Data will be obtained in eCRFs from a combination of national registers and medical records. Bedside target list for treatment reasons and decisions will be implemented in the PDMS (*) at each site, if possible.

Baseline variables

- National identification number (if available)
- Sex
- Age at randomization
- Estimated height
- Measured (if not possible estimated) weight
- Comorbidities? Y/N (hypertension*, chronic heart failure*, previous myocardial infarction, previous stroke, chronic obstructive pulmonary disease*, diabetes*, hematological malignancy*, metastatic cancer*, AIDS*)
- Elective or emergency admission*
- Operative or non-operative admission*
- Site of infection (pulmonary/abdominal/urinary tract/soft tissue/other)
- Previous plasma/serum creatinine (7–365 days before hospital admission), if available

24-h from ICU admission:

- Values for Simplified Acute Physiology Score (SAPS II)*

Twenty-four hours before randomization

- Volume of resuscitation fluids (crystalloids, colloids and blood products specified in milliliters)
- Hemoglobin (lowest)*
- SOFA score *variables**

At randomization

- Norepinephrine dose and mean arterial pressure (MAP) at the same time
- Total fluids given in last 2 h
- Lactate (last value from the previous 2 h)

Continuously as 10-min medians in the first 72 h after randomization:

- Systolic arterial pressure*
- Mean arterial pressure*
- Central venous pressure*
- Heart rate*
- Peripheral oxygen saturation (SpO_2_)*
- Continuous central venous oxygen saturation, if available
- Continuous mixed venous saturation, if available
- Dose of norepinephrine*
- Dose of dobutamine*

One-hour intervals (for 72 h)

- Urinary output*
- Volume of given fluids
- CRT – only in the TTP group
- Assessment of upper arm temperature – only in the TTP group
- Assessment of skin mottling score – only in the TTP group

Two-hour intervals (for 72 h unless study endpoint reached)

- Arterial lactate measured in both groups

Four-hour intervals during the first 72 h after randomization (if not discharged from the ICU)

- Arterial blood gas tensions (PaO_2_, PaCO_2_), pH and base excess (BE)
- Calculated Mixed v-aCO_2_/Da-vO_2_-ratio (if pulmonary artery catheter, PAC)
- Cardiac index (if PAC)
- Stroke index (if PAC)

Daily in the first 7 days after randomization (if not discharged from the hospital):

- SOFA score variables*
- Total volume of fluids
- Estimated fluid balance

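### The primary Mann-Whitney test ignores the randomization strata, although a stratified version is already planned: a modest loss of efficiency, not a validity error

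*Protocol article*

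**What the plan says.** All references are to the protocol article.

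- **Randomization:** "The patients will be stratified according to the site and presence/absence of chronic hypertension". Methods/design says the same.
- **Appendix 5:** the primary analysis of the primary outcome, and of secondary outcomes b, c, d, e, f, h, i and j, "will be an unadjusted Mann-Whitney test". Statistical methods also names the Mann-Whitney test as primary.
- **Appendix 5, sensitivity analysis:** the p "values will be recalculated using permutations within groups defined by site and the presence/absence of hypertension", with 100,000 permutations per test.
- **Appendix 5, other models:** the Cox model for time to lactate normalization is adjusted for site and hypertension, and so are the logistic and Cox models for 90-day survival.
- **Sample size and power:** the simulation behind Table 1 uses a Mann-Whitney test and mentions no strata or covariates.
- **Appendix 4, values recorded at randomization:** "Lactate (last value from the previous 2 h" and "Norepinephrine dose and mean arterial pressure (MAP) at the same time". No analysis of the primary outcome uses them as covariates.

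The article gives no reason for leaving the strata out of the primary test.

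**The concern.** Blocked randomization within strata balances the arms within each stratum, so differences between strata contribute almost nothing to the error of the treatment comparison. An unadjusted rank test still counts those differences in its variance. If the strata are prognostic, the test uses too large a standard error: its type I error falls below 5 % and some power is lost.

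That the strata are prognostic is plausible here. Table 2 sets different MAP targets for previously hypertensive patients in both arms, and the primary outcome counts time free of vasopressors. Interventions are at the clinicians' discretion, so practice may also differ between sites.

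The plan is uneven on this point: it adjusts for both factors in its models for other endpoints but not in its primary test. It already contains the test that would cure this, in second place.

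**Working it through.** **1. The plan's own figure.** Inputs from Sample size and power: 25 % deaths with value 0; survivors' value is 720 h minus a log-normal time with mean 70 h (control) or 70 − 18 = 52 h (TTP), SD 30; Mann-Whitney test. The 0.05 level was taken as two-sided. The log-normal parameters follow from σ² = ln(1 + (SD/mean)²) and μ = ln(mean) − σ²/2:

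- control: σ² = ln(1 + (30/70)²) = 0.169, μ = 4.164
- TTP: σ² = ln(1 + (30/52)²) = 0.287, μ = 3.808

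Simulated power is 0.788 at N = 194 (40,000 runs) and 0.801 at N = 200. Table 1 gives 194 for 80 %, so the figure is reproduced for the unadjusted test.

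**2. Expected effect of ignoring the strata.** Let η² be the share of the rank variance that lies between strata. No value is given, so it is assumed. With stratified randomization the true variance is about (1 − η²) times the one the unadjusted test uses. With z values 1.96 and 0.84, and the design set to 80 % power by the unadjusted formula:

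- type I error, unadjusted: 2Φ(−1.96/√(1 − η²))
- power, unadjusted: Φ(0.84/√(1 − η²))
- power, stratified: Φ(2.80/√(1 − η²) − 1.96)

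| Assumed η² | Type I error, unadjusted | Power, unadjusted | Power, stratified | Difference (points) |
|---|---|---|---|---|
| 0 | 0.050 | 0.800 | 0.800 | 0 |
| 0.05 | 0.044 | 0.806 | 0.820 | 1.4 |
| 0.10 | 0.039 | 0.813 | 0.840 | 2.7 |
| 0.20 | 0.028 | 0.827 | 0.880 | 5.3 |

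**3. Simulation with weak strata.** N = 194, the plan's outcome distributions, four equal sites by hypertension (50 %), blocks of 4 and 6, 4,000 runs. The stratified test is the normal approximation to the within-stratum permutation test on ranks. The correlations are between each factor and a latent outcome score.

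| Site / hypertension | Unadjusted | Stratified |
|---|---|---|
| 0 / 0 | 0.792 | 0.789 |
| 0.1 / 0.1 | 0.802 | 0.805 |
| 0.2 / 0.1 | 0.795 | 0.800 |
| 0.2 / 0.2 | 0.799 | 0.815 |

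The gain is 0 to about 2 points.

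**4. Simulation with stronger strata.** N = 200, with site and hypertension affecting both death and shock duration. This is a different scale from step 3, and only comparisons within a row are meaningful.

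| Assumed effects | Power, unadjusted | Power, permutation | Type I error, unadjusted | Type I error, permutation |
|---|---|---|---|---|
| 0.2 / 0.2 | 0.826 | 0.851 | 0.038 | 0.050 |
| 0.3 / 0.2 | 0.836 | 0.874 | 0.035 | 0.050 |
| 0.3 / 0.3 | 0.852 | 0.899 | 0.026 | 0.044 |

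The gain is 2.5, 3.8 and 4.7 points. The van Elteren test gave 0.852, 0.883 and 0.917 in the same rows. Where the strata were not prognostic it cost about 1 point (0.791 against 0.803 unadjusted), while the permutation test cost nothing (0.804).

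**5. Baseline covariate (optional part).** Same set-up as step 3, with non-prognostic strata and one covariate explaining R² of the outcome ranks; rank-based covariance adjustment against the unadjusted test. The R² values are assumed.

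| R² | Unadjusted | Adjusted |
|---|---|---|
| 0.04 | 0.781 | 0.794 |
| 0.08 | 0.782 | 0.816 |
| 0.14 | 0.784 | 0.842 |
| 0.22 | 0.793 | 0.870 |

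The gain is about 1 to 8 points. Equivalently, the N for equal power is about 194 × (1 − R²): 185 for R² = 0.05, 175 for 0.10 and 156 for 0.20.

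**The case against.** The strongest reply is that nothing here is wrong. The unadjusted test is valid, its type I error is at or below nominal, and the sample size was simulated for this same test. The stratified test is pre-specified for every Mann-Whitney outcome, so the reader of the results will see it. Statistical methods also plans analyses in patients with and without hypertension. If the planning inputs fail, the blinded recalculation after 150 patients can raise the sample to 300. All of that stands, and it makes this an efficiency point. It does not explain why the less efficient of two planned tests should be the one that decides the trial.

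Three stronger readings are tempting, and the document does not support them.

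- *The trial is underpowered because of this choice.* At the stated inputs it is not, as step 1 shows. Whether those inputs are optimistic is a separate question.
- *The unadjusted test is conservative as such.* It is so only if the strata are prognostic, and no stratum differences are given.
- *Strong baseline predictors are being wasted.* The Background only calls raised lactate a marker of poor prognosis, and no strength is given for any variable. Inclusion requires lactate of at least 3.0 mmol/L and vasopressor use, which narrows the range of both covariates. Patients may also qualify on epinephrine or vasopressin, so norepinephrine dose measures severity incompletely.

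It is also fair to object that covariate adjustment is more than a change of wording. The imputation model in Appendix 5 lists outcomes, sex, age, stratification and treatment variables, but neither baseline lactate nor norepinephrine dose. The power calculation would also no longer match the primary test exactly.

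**Conclusion.** The point holds as a modest, avoidable loss of efficiency. The primary test does not follow the randomization, the plan's own models for other endpoints do, and no reason is given. Validity and the stated 80 % power are not in question.

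The size rests on assumptions. From the strata alone the loss is nil if they are not prognostic and about 0 to 5 points for the permutation test over the effects examined. A baseline covariate could add about 1 to 8 points for an assumed R² of 0.04 to 0.22. Confidence in the direction is high, given prognostic strata; confidence in the amount is limited. The change is worth making because the permutation test cost essentially nothing where the strata carried no information.

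**What to change.** **Main change, before un-blinding.** In Appendix 5 and Statistical methods, name the planned permutation test within site-by-hypertension strata as the primary analysis of the primary outcome and of secondary outcomes b, c, d, e, f, h, i and j. Keep the unadjusted Mann-Whitney test as the sensitivity analysis. A van Elteren test is an acceptable alternative; the permutation test has the advantage of being specified already. The cost is to exchange the roles of two planned analyses. No new data are needed. Recruitment has begun, so the change should be dated and recorded as made without knowledge of treatment allocation.

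**Optional.** Pre-specify rank-based covariance adjustment for lactate at randomization, and possibly norepinephrine dose. Both are already recorded. The cost is small: add these covariates to the multiple-imputation variable list, and note beside Table 1 and the blinded recalculation that a power calculation for the unadjusted Mann-Whitney test is then slightly conservative.

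### The listed imputation variables include no baseline severity measure, so an imputed primary result could keep a bias if loss tracks severity differently by arm and a patient's outcomes are missing together

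*Protocol article*

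**What the plan says.** Appendix 5 (the detailed statistical analysis plan) sets the trigger: "If any of the tests presented above must be based on data with more than 5 % missing multiple imputation will be employed". Once one test meets it, "all tests will be conducted both as complete case analysis and multiple imputation", but "only for tests based on data with more than 5 % missing will the multiple imputation approach constitute the primary analysis". The software is named ("The multiple imputation will be conducted in R using the mice package"), with a reference to that package's documentation. The variables are then listed: "All outcome variables (secondary and primary), sex, and age as well as stratification and treatment variables will be included in the multiple imputations procedure". The stratification variables are site and chronic hypertension.

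Appendix 4 shows what else is available. At randomization it records "Norepinephrine dose and mean arterial pressure (MAP) at the same time" and the last lactate from the previous 2 h. For the 24 h before randomization it records SOFA variables. SAPS II is recorded for the 24 h from ICU admission.

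The primary analysis of the primary outcome "will be an unadjusted Mann-Whitney test". The effect size is the difference in raw means with a bootstrap interval. The stratified permutation test is a sensitivity analysis: "As a sensitivity analysis the *p* values will be recalculated using permutations within groups defined by site and the presence/absence of hypertension".

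**The concern.** Multiple imputation repairs selective loss only to the extent that the imputation model holds the variables that drive both the loss and the outcome. In septic shock these include illness severity at entry. If all of a patient's outcomes are missing, the listed model has only age, sex, site, hypertension status and arm to work from. The imputed value is then close to a draw from the observed patients of that arm, whatever the patient's lactate or vasopressor dose at entry.

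The trial is open label and uses deferred consent in part, so loss that relates to severity differently in the two arms is conceivable. Above the 5 % threshold the imputed result is the headline result, so any remaining bias would sit in the primary analysis.

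**Working it through.** **Inputs from the article.** Mortality is 25 % in both arms, and deaths score zero. Hours with vasopressors or hyperlactatemia in survivors are log-normal with mean 70 h and SD 30. The mean primary outcome in survivors is 650 of 720 h. The tested difference is 18 h in survivors, or 0.75 × 18 = 13.5 h over all patients. At least 200 patients are planned.

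**Inputs assumed.** Missing fraction 6, 10 or 20 %; the strength of the link between severity and outcome; the missingness mechanism; 1:1 allocation; a two-sided 0.05 level.

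**Reproducing the plan's figure.** Simulating Table 1's cell for 25 % mortality and 18 h (N = 194, Mann-Whitney) gives power 0.790, within 2 points of the stated 80 %. The endpoint model used below is therefore the plan's own.

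**Why a bias can arise.** Let a fraction f of one arm be missing. The true arm mean is (1 − f)·μ_obs + f·μ_mis. An imputation that cannot see severity sets μ_mis close to μ_obs, so the error is f·(μ_obs − μ_mis). If the gap is mainly mortality, μ_obs − μ_mis ≈ 650 × (difference in mortality between missing and observed patients). At f = 0.10:
- an error of 5.2 h needs a gap of 52 h, or 52/650 = 8 points of mortality;
- an error of 15.3 h needs 153 h, or 153/650 = 24 points.

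**Simulation 1** (400,000 per arm, 10 % missing per arm, no other outcome informative, log-odds ratio for death of 0.5 / 0.8 / 1.0 per SD of severity). With severity omitted, the mean difference is off by 5.2 / 8.0 / 10.1 h when loss tracks severity in one arm only. It is off by 10.4 / 16.4 / 19.6 h when the arms have opposite patterns. With severity included, it is off by no more than 0.3 h.

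**Simulation 2** (N = 200, true difference 0 h, latent severity correlated 0.6 with death risk and with shock hours, predictive mean matching, M = 20, 600 trials per setting). Entries are the shift in mean difference against the same trials with full data, with the rejection rate of the pooled Mann-Whitney test in brackets.

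| Loss tied to severity | Missing | Severity omitted, no other outcome informative | Severity omitted, death carried | Severity and death included |
|---|---|---|---|---|
| Same in both arms | 6 % | −0.2 h (4.3 %) | +0.1 h (5.2 %) | +0.1 h (5.5 %) |
| | 10 % | −0.4 h (5.3 %) | +0.1 h (5.2 %) | +0.1 h (5.7 %) |
| | 20 % | +0.4 h (4.3 %) | +0.1 h (4.2 %) | +0.1 h (4.7 %) |
| One arm only | 6 % | +8.9 h (5.5 %) | +0.6 h (4.3 %) | +0.1 h (4.3 %) |
| | 10 % | +15.3 h (6.0 %) | +0.9 h (6.0 %) | +0.1 h (5.5 %) |
| | 20 % | +26.5 h (9.0 %) | +1.6 h (6.8 %) | +0.1 h (6.2 %) |
| Opposite in the arms (extreme) | 6 % | +12.7 h (7.7 %) | +1.0 h (5.3 %) | 0.0 h (3.5 %) |
| | 10 % | +24.1 h (13.3 %) | +1.7 h (8.0 %) | +0.1 h (6.0 %) |
| | 20 % | +45.6 h (23.5 %) | +3.3 h (10.8 %) | +0.2 h (5.0 %) |

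Example: one arm, 10 %, severity omitted gives 12.9 − (−2.4) = 15.3 h. The complete-case shift there is 12.7 − (−2.4) = 15.1 h, so in this situation the imputation repairs nothing. Monte Carlo error is about 1.7 h on each mean difference (less on the within-trial shifts) and about 1 point on rejection rates near 5 %. The sign of the bias depends on which arm loses its sicker patients.

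**Pooling.** The Mann-Whitney test has an estimate, θ = P(TTP > MCG) + ½P(tie), with a variance. Rubin's rules give the mean of θ over the M data sets and total variance W + (1 + 1/M)·B, where W is the within-imputation and B the between-imputation variance. This ran in every simulated data set. With severity and death in the model, null rejection was 3.5 to 6.2 %.

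**The case against.** The strongest reply is that the list already holds all secondary outcomes. The days-alive measures among them carry death, which dominates the endpoint. The simulation supports this: with death carried, the shift is at most 1.6 h in the one-arm case and 3.3 h in the most extreme setting. This stands wherever those outcomes are observed. It fails when they are missing together with the primary outcome. Death is also not clearly listed in its own right. The Statistical methods section counts day-30 mortality among the secondary outcomes, the Secondary outcome measures list has no such item, and 90-day mortality is exploratory.

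The triggering conditions may also never occur. Withdrawn patients are followed and analysed by intention to treat, and vasopressor use is recorded daily to day 30. Death is taken from registries (for the exploratory outcome, and not in Switzerland), and complete-case results are reported alongside. Nothing in the article points to more than 5 % missing or to loss that differs by arm. If a refused deferred consent removed all of a patient's data, baseline severity would be lost as well. The list says what will be included and does not say that nothing else may be. All of this stands and keeps the point small.

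The primary test is also less sensitive than the mean. In the one-arm case at 10 % missing, rejection is 6.0 % against 5.3 % with full data. The damage falls mainly on the reported mean difference.

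A reader might infer that rank, exact and permutation tests leave nothing to pool, so that the imputed primary analysis cannot be computed. The documents do not support this. The win probability and the plan's own mean difference can both be pooled, the permutation test is a sensitivity analysis only, and the article states no invalid rule such as averaging p values. An unwritten combining rule is missing detail that an article may leave to a fuller document.

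**Conclusion.** The point holds as a conditional weakness of low severity. The stated list omits the severity measures that the trial collects at or before randomization, and the imputed analysis can become primary. The mean difference is then at risk by roughly 5 to 15 h at 6-10 % missing, against a 13.5 h target, under three conditions: missingness depends on severity, it does so in one arm only, and a patient's outcomes are missing together. Opposite patterns in the two arms give more, but that is an extreme case. If death status is carried, the shift is at most about 3 h. If the pattern is the same in both arms, it is about zero.

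The missing fractions, the severity-outcome link and the mechanisms are assumptions, as the article gives none of them. The finding is not that the imputed analysis will be biased, nor that it cannot be carried out.

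**What to change.** Add to the listed imputation variables lactate at randomization, norepinephrine dose at randomization and the pre-randomization SOFA variables, and name 30-day death status explicitly. SAPS II should serve at most as an auxiliary variable. Its window runs 24 h from ICU admission and randomization is due within 8 h of admission, so at least 24 − 8 = 16 h of it can fall after randomization in an open-label trial.

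As a minor clarification, state that the Mann-Whitney win probability (for example on the logit scale) and the mean difference are pooled by Rubin's rules, with the p value taken from the pooled win probability.

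The cost is a few more variables in the imputation call and one sentence on pooling. No new data are needed, and the change can be made before unblinding.
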